## Abstract

**Background:**

Emotion regulation is a key transdiagnostic risk factor for a range of psychopathologies, making it a prime target for both prevention and treatment interventions in childhood. Existing interventions predominantly rely on workshops or in-person therapy-based approaches, limiting the ability to promote emotion regulation competence for children in everyday settings and at scale. Purrble is a newly developed, inexpensive, socially assistive robot—in the form of an interactive plush toy—that uses haptic feedback to support in-the-moment emotion regulation. It is accessible to children as needed in their daily lives, without the need for a priori training. Although qualitative data from previous studies show high engagement in situ and anecdotal evidence of the robot being incorporated into children’s emotion regulation routines, there is no quantitative evidence of the intervention’s impact on child outcomes.

**Objective:**

The aim of this study is to examine the efficacy of a new intervention model for child-led emotion regulation—Purrble—that can be deployed across prevention and treatment contexts.

**Methods:**

Overall, 134 children aged 8 to 10 years will be selected from an *enriched* nonclinical North American population; for inclusion, the cutoff for the parents’ rating of child dysregulation will be ≥10 points in the total difficulties score on the Strengths and Difficulties Questionnaire. This cutoff was selected to obtain a measurable, but not necessarily clinical, level of the child’s emotion regulatory difficulties. The selected families will be randomly assigned with .5 probability to receive either a Purrble or an active control (noninteractive plush toy). The primary outcome will be a daily ecological momentary assessment measure of child emotion regulation capability (as reported by parents) over a period of 4 weeks. Exploratory analyses will investigate the intervention impact on secondary outcomes of child emotion regulation, collected weekly over the same 4-week period, with follow-ups at 1 month and 6 months postdeployment. Quantitative data will be analyzed on an intent-to-treat basis. A proportion of families (approximately 30% of the sample) will be interviewed after deployment as part of the process analysis.

**Results:**

The study is funded by the UKRI Future Leaders Fellowship (MR/T041897/1) and an in-kind contribution from the Committee for Children. This study received ethical approval from the Pearl institutional review board (#18-CFC-101). Participant recruitment started in February 2021, with the 1-month deployment in April-May 2021. The results of this analysis will be published in 2022.

**Conclusions:**

This study will be the first quantitative evaluation of the efficacy of an innovative, proof-of-concept intervention model for an in situ, child-led emotion regulation intervention. Insights into the trajectory of daily changes, complemented with weekly questionnaire batteries and postdeployment interviews, will result in an in-depth understanding of whether and how the hypothesized intervention logic model works, leading to further intervention optimization.

**Trial Registration:**

ClinicalTrials.gov NCT04810455; http://clinicaltrials.gov/ct2/show/NCT04810455

**International Registered Report Identifier (IRRID):**

PRR1-10.2196/28914

## Introduction

Maladaptive emotion regulation in childhood is associated with an increased incidence of both internalizing and externalizing mental health disorders [1-4]. In contrast, adaptive emotion regulation in childhood is associated with better mental [5-7] and physical health [8-10]. For these reasons, emotion regulation in childhood is a crucial target for treatment and prevention programs to reduce the societal and personal burden of mental health disorders [11,12].

Although emotion regulation (ER) skills are malleable, and a range of predominantly adult-focused interventions have started to appear in clinical settings (eg, Emotion Regulation Therapy [13] and the Unified Protocol for Transdiagnostic Treatment of Emotional Disorders [14,15]), existing work shows that children’s ER skills are difficult to shape and maintain without detailed guidance and support [16-18]. This work has also shown that parenting strategies play a key role in shaping and maintaining children’s patterns of ER [19-27], but requiring parents’ involvement in existing training, such as in-person workshops, represents yet another barrier to treatment because of well-known issues with access, reach, and cost of parent training programs.

However, the field lacks evidence-based intervention mechanisms to deliver cost-effective ER interventions for children directly in situ, relying instead on extensive in-person workshops (prevention context) or clinical sessions for children and parents (treatment context). Existing approaches thus lead to high costs that disproportionately disadvantage underprivileged families, who would likely benefit most; such families face access- and time-based challenges to take part in available intervention programs [28], although children from low socioeconomic status populations are at risk of low emotion-regulation competencies already at an early age [29], and the gap further widens over the school years [30].

To address the challenges outlined, we developed a proof-of-concept intervention platform to deliver in situ support for child ER during everyday emotionally charged situations, such as the child feeling angry, anxious, or sad. On the basis of a 2-year-long development [31,32], we worked with children, parents, and prevention science experts to co-design an intervention that would support children in strengthening their ER skills. The research prototype was then produced by the Committee for Children (a US-based nonprofit developer of socioemotional learning programs) and Sproutel [33], resulting in a commercial-grade therapeutic toy called Purrble [34].

The initial research prototypes were designed as the first instantiation of a novel *situated* intervention model, which is delivered through an interactive, socially assistive robot sent home with the child or used in schools, without any previous training for either the child or their parent or caregiver. As such, the psychological effects of Purrble are assumed to arise from repeated *bottom-up* support in situ, instead of relying on the traditional *top-down* training contexts delivered through workshops or therapy sessions. In particular, the intervention logic model relies on a 3-stage approach: (1) enabling the child to downregulate emotional moments in situ can (2) provide a preferred alternative to maladaptive emotion regulatory strategies (eg, rumination or suppression) and, over time, (3) lead to shifts in child ER competence [31]. For a detailed description of the hypothesized mechanisms and their links to the intervention design choices, see the *Intervention* section.

To date, 2 qualitative deployment studies have investigated the engagement and acceptability of the prototype in young children’s homes, as well as subjective indicators of effects on emotion regulatory practices (whether positive or negative), as reported by parents and children [31,32]. Findings from these studies have been very positive: all 25 children engaged with the prototype throughout the deployments, all wanted to keep it for longer, and all described how they naturally incorporated it into their everyday routines and gravitated toward it when they needed to downregulate their emotions, including anger, anxiety, or just needing to relax.

Although these early data are promising, we lack quantitative data on the impact of the intervention on child outcomes. In particular, evidence is needed to (1) evaluate the efficacy of Purrble in delivering measurable changes in emotion regulatory practices of children over time and (2) start validating the hypothesized intervention logic model. This study aims to fill these evidence gaps.

## Methods

### Study Design and Objectives

The objective of this study is to evaluate the impact of having access to the Purrble intervention, compared with an active control in the form of a noninteractive plush toy, on child daily ER (primary outcome) as well as a range of secondary outcomes over 1 month.

The study is a 2-arm, exploratory randomized controlled trial comparing an intervention group (Purrble) with an active control group (noninteractive plush toy). The deployment period will be 4 weeks and will include daily parent self-report measures via ecological momentary assessment (EMA), as well as weekly validated surveys with a 1-month and 6-month follow-up (see Figure 1). The intervention period will start immediately after children receive their arm-appropriate toys. Participants in both the intervention and active control groups (Figure 2) will be able to keep the toys after the deployment period ends. Active control group participants will not be offered Purrble units postdeployment, as this would unblind the conditions before follow-up data collection.

**Figure 1 figure1:**
[figure not shown]
Assessment design. EMA: ecological momentary assessment; ERC: Emotion Regulation Checklist; SDQ: Strengths and Difficulties Questionnaire; TWEETS: Twente Engagement With eHealth Technologies Scale.

**Figure 2 figure2:**
[figure not shown]
Participant selection flowchart.

### Intervention

We hypothesize that engagement with an in situ, *bottom-up* ER intervention that enables in-the-moment soothing for children will lead to measurable changes in child self-regulatory behaviors over time.

#### Purrble—Intervention Design and Logic Model

The intervention takes the form of an interactive plush toy (Figure 3), which was designed to be handed over to the child and support in-the-moment soothing (see Theofanopoulou et al [31] and Slovak et al [32] for the design and data from previous deployments).

**Figure 3 figure3:**
[figure not shown]
Purrble plush toy.

The toy is introduced to the child as an anxious creature that needs attention from humans, such as soft stroking and hugging. Embedded electronics enable the toy to produce vibration patterns that simulate a heartbeat (ranging from frantic to slow and steady). When picked up, the toy emits a frantic heartbeat that slows down if the child uses calm stroking movements, as registered by the embedded sensors. If the toy is soothed for long enough, the prototype transitions into a purring vibration indicating a calm, contented state. The minimum time for this transition is less than 1 minute, but the transition can take longer depending on the child-specific interactions with the prototype.

The logic model underlying the intervention is assumed to operate on 3 levels building on each other—see the study by Theofanopoulou et al [31] for more details:

Level 1 pertains to *directly providing in-the-moment soothing support to children in naturally occurring emotional moments* when they would attempt to calm down. The toy’s physical and interaction design was aimed at tapping into various known regulatory factors, grounded theoretically in the Gross extended process model of ER [35]. Specifically, we designed the prototype interaction with the aim to impact 2 separate stages of the ER process: the *attentional deployment stage* [36-39], by shifting children’s attention from the emotion-eliciting situation toward interacting with the toy, and the *response modulation stage*, by facilitating down-regulation through pleasant tactile interaction analogously to the mechanisms presumed to underpin emotion regulatory effects of human-animal interaction [40-45].Level 2 is concerned with mechanisms that *facilitate children’s long-term engagement* with the intervention, building on the positive subjective experience of in-the-moment soothing. The framing of the toy as an *anxious creature in need of assistance* is the hypothesized key driver; we assume that this will not only frame the interactions regarding helping regulate others’ emotions (extrinsic ER; [41,46,47]) but also facilitate the creation of a sense of relationship and responsibility for the well-being of the creature, similar to the long-term engagement seen with child-orientated robots [48] or products such as Tamagotchi [49-51].Finally, level 3 is assumed to emerge from repeated experiences of soothing interactions over time, leading to a *shift in children’s ER practices and implicit beliefs about emotion* (ie, the individual’s beliefs about whether emotions can be regulated; see study by Ford and Gross [52] for details). Specifically, we hypothesize that repeated interactions with the toy will result in a shift in children’s implicit beliefs about the controllability of emotion [52,53], a well-known target for intervention [54-58], as well as help reduce maladaptive ER patterns such as rumination or suppression [59].

Deployments with the research prototypes underpinning the current Purrble [31,32] show that, across all 25 families, children reported that the smart toy was incorporated into the children’s ER practices and engaged with naturally in moments the children wanted to relax or calm down. Specifically, the data from [31] shows that the children interacted with the toy throughout the week-long deployment (eg, average active use for 74.9, SD 64.1 minutes per day; median 60.5), they found the experience enjoyable, and all children requested to keep the toy longer. Children’s emotional connection to the toy appears to have driven this strong engagement. Parents reported satisfaction with and acceptability of the toy. No quantitative data on changes in ER were collected in previous studies because of the small sample size and the focus on feasibility and understanding of appropriation within families.

#### Active Control Group

When compared with a traditional noninteractive plush toy, the intervention model underpinning Purrble includes 2 possible pathways through which the effects should occur:

The first is the in-the-moment soothing support (level 1 in the logic model) that we hypothesize is driven by the interactivity of the toy. The lack of such situated down-regulation support should thus be the key difference between the intervention and an active control, that is, a noninteractive stuffed toy, leading to lower engagement over time (level 2) and a lack of impact on child ER practice (level 3).However, an alternative pathway is the ER routines (levels 2 and 3 in the logic model) that could, in principle, emerge around the intervention narrative of a physical object to use for calming down, even without the toy being interactive. In other words, if it was simply the narrative of an anxious creature in need of care (rather than the combination of the narrative together with the interactivity) that drives long-term engagement and changes in behavior, a noninteractive stuffed toy could still lead to the development of the same routines. We see this as an unlikely scenario, for example, given the prevalence of plush toys in most, if not all, households—but one that should be addressed in the study design.

For these reasons, we argue that a comparison with a nonactive control—such as waiting list or treatment-as-usual (ie, nothing)—would not allow us to distinguish the hypothesized impact on in-the-moment soothing of interactivity versus the emergence of new family routines and would also be open to unequal social desirability bias. However, from the perspective of the hypothesized logic model, it is not necessary for the active control to have exactly the same form factor as the active toy, as long as it is comparable in size, shape, and appeal. In fact, we have explicitly decided not to use deactivated Purrble units as active controls because of the increased risk of unblinding, whereby the participants search for or come across Purrble on the web (or notice the plastic enclosure with electronics inside the toy) and assume that their unit is malfunctioning.

#### Selection and Validation of Active Control Units

The selected active control toy is the *Wild Republic 8″ Hedgehog animal*. The selection process was guided by the following requirements: the plush toy needed to have analogous size, weight, and quality of materials, and at least similar (if not higher) visual appeal. We also made sure to include the design characteristics that our previous work suggested were important for the narrative around the toy [31,32]. These included selecting a similarly stylized animal (to enable emotion projection and feelings of care), as well as no visible mouth on the toy (to prevent setting an expectation about the toy’s emotional state as a mouth would imply an emotional expression). In addition, we have adapted the one-page parent-facing descriptions of the narrative that come with Purrble also for the active control unit; as such, the active control families will receive the same general narrative—including that the creature is anxious and needs human care, but without the explicit mentions of the toy interactivity—and the same suggested activities for parents.

To validate that the active control is at least as visually appealing as the intervention, we ran a web-based experiment in which participants were randomly assigned to rate either the Hedgehog or the Purrble images. In both cases, the prompts were professional photos from the front and side on a white background, presented at equal size (Figure 4). The experiment was powered to detect a medium-sized effect (*d*=0.4) at 80% power for a comparison on a single measure, resulting in a sample size of 200 (1:1 allocation ratio). Participants were recruited through the web-based research platform Prolific, with the survey hosted by Qualtrics (including blocked randomization). Inclusion criteria for parents were the eldest child born in 2010-2013 (approximately aged 8-10 years), country of residence in the United Kingdom or the United States, and above 95% acceptance of tasks on Prolific. The participants were prompted to imagine that their oldest child had received the plush toy pictured above as a present. We then asked 3 questions, with the first question—appeal—preselected as the primary measure: (1) How appealing do you yourself find the toy? (2) How appealing do you think your child would find the toy? and (3) How likely would you be to recommend this toy to another parent?

**Figure 4 figure4:**
[figure not shown]
On the left, an image of the Hedgehog toy for the active control group. On the right, an image of Purrble for the intervention.

The results show that the hedgehog was consistently rated higher than Purrble on all 3 questions (Figure 5). This suggests that, if anything, the active control should be more appealing to our study participants than the intervention units: it is a particularly stringent control condition to test the effect of a visually appealing, but noninteractive, plush toy. In other words, if it was purely the visual appeal of the units that would drive child or parent engagement and the resulting ER effects (as opposed to the interactivity of the intervention units), we would expect the active control to show at least as good if not better engagement and reports of changes in child ER from the families.

**Figure 5 figure5:**
[figure not shown]
Rating of the questions regarding the appeal of Purrble versus the active control unit, and the likelihood of recommending Purrble versus the active control unit to another parent.

### Participant Eligibility Criteria

Given Purrble’s intended use as a targeted prevention intervention, we will recruit an *enriched* population of neurotypical children, aged 8-10 years, from families in the United States. The enrichment consists of recruiting families where the child is seen as struggling with some level of ER difficulty (as reported by their parent) but is not undergoing clinical treatment.

The specific inclusion criteria were a child aged 8-10 years, parent-reported score of ≥10 for the total difficulties score on the Strength and Difficulties Questionnaire (SDQ). The exclusion criteria for the child were current participation in another mental health intervention. In addition, an exclusion criterion for the parent and/or the child is not being fluent in English (as all measurement scales are in English).

The target child age range has been selected as collecting self-report measures from young children is a well-known challenge, especially when inquiring about complex cognitive concepts such as those involved in ER [60,61], and our pilot work in families and schools suggests that acceptability for the toy is high with children of this age, with children aged 8-10 years still using the toy as intended.

### Recruitment, Randomization, and Blinding

Parents will be recruited by sending the study invitation to a mailing list of approximately 10,000 parents or guardians, whose children are receiving Committee for Children programs in school, and who have signed up to receive information from the Committee for Children.

Once eligibility is proven and parents fill out the baseline questionnaires, families will be randomly assigned to the intervention or active control group. Families will be randomized using a computerized algorithm and randomly permuted block sizes. The allocation schedule is generated by a Committee for Children researcher not directly involved in the data collection (and not aware of participants’ details apart from their address) and is unknown to the investigator and the participants. The principal investigators will not be aware of the allocation until data collection is complete.

Blinding is present: the families will not be aware of the existence of another condition throughout the study, requiring the participation cap on students from any single class.

### Outcome Measures

The primary outcome will be a daily EMA measure of child emotion regulation capability (as reported by parents) over a period of 4 weeks. Exploratory analyses will investigate the intervention impact on secondary outcomes of child emotion regulation, collected weekly over the same 4-week period, with follow-ups at 1 month and 6 months postdeployment. See Table 1 for a summary of the outcome measures and assessment times.

**Table 1 table1:** Summary of the outcome measures and assessment times.

Outcome measure	Baseline	Deployment				Follow-up			
		Week 1	Week 2	Week 3	Week 4	1 week	2 weeks	1 month	6 months
Perceived child ER ability		Collected daily	Collected daily	Collected daily	Collected daily				
Daily parent report ecological momentary assessment (modified differential emotions scale)		Collected daily	Collected daily	Collected daily	Collected daily				
Daily parent report ecological momentary assessment (engagement)		Collected daily	Collected daily	Collected daily	Collected daily				
Daily parent report ecological momentary assessment (reaction to triggers)		Collected daily	Collected daily	Collected daily	Collected daily				
Weekly parent questionnaire (Strength and Difficulties Questionnaire)	✓	✓	✓	✓	✓			✓	✓
Weekly parent questionnaire (ER Checklist)	✓	✓	✓	✓	✓			✓	✓
Weekly parent questionnaire (Twente Engagement With eHealth Technologies Scale)		✓	✓	✓	✓			✓	✓
Weekly children questionnaire (Difficulties in ER Scale)	✓	✓	✓	✓	✓			✓	✓
Weekly children questionnaire (emotion regulation-beliefs)	✓	✓	✓	✓	✓			✓	✓
Interviews with families						✓	✓		

#### Primary Outcome Measure

The primary outcome measure will consist of a composite end-of-day 4-item parent report measure of the *perceived child ER* ability throughout the day. The specific items are listed below, all measured as a visual analog scale [62,63] with *not at all* and *very much so* as the anchors. The composite score for each day will be computed as the mean value across the 4 items:

Today, to what extent was your child able to take difficult things in a stride?Today, to what extent did your child get easily triggered or upset? (reverse-scored)Today, to what extent was your child able to calm down easily if upset?Today, to what extent did your child get very emotional even after the littlest things? (reverse-scored)

Specifically, this EMA item composite aims to indirectly tap into day-to-day changes in a child’s ability to downregulate their emotions after (and thus cope with) triggering situations they routinely experience in their daily life. Our expectation is that contact with the Purrble will lead to the following:

Lower intensity negative emotions after facing everyday stressors (eg, by being able to downregulate before emotional response escalate—cf, level 1 in the theory of change).Briefer duration of negative emotions after facing everyday stressors (eg, being able to downregulate emotions faster with Purrble—cf, levels 1 and 3 in the theory of change).

By being measured repeatedly over time and within subjects, the items capture the changes in emotional outcomes that would indicate changes in the child’s ER ability, assuming that the trait-based reactivity to daily stressors remains stable. The items were thus selected to tap into the proximal outcomes of ER behavior that (1) would be affected if the intervention is effective, (2) is directly observable by parents, (3) is state-based (rather than trait-based) to enable daily measurement, and (4) is connected to the intervention theory of change.

The item selection drew on a range of established measures of emotion dysregulation (Strengths and Difficulties Questionnaire, SDQ [64], Emotion Regulation Checklist, ERC [65], Difficulties in Emotion Regulation Scale (DERS) [66], and Children’s Emotional Management Scales [67]), as well as qualitative data from previous deployments [31,32] with parental reports of increased emotion regulation after potentially triggering events being the common theme.

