#### Data Analyses

All analyses of daily EMA outcomes (the primary outcome of daily ER and secondary outcomes of engagement with the toy and mood), as well as the analyses of the weekly outcomes, will be conducted using random-effect models for longitudinal regression. These models consider the nested nature of repeated-measures data and are robust to data missingness and violations of the normality assumption. The regression models will examine the difference in the outcome as a function of the assigned condition (Purrble vs active control). The models will adjust for the baseline levels of the score on the total difficulty scale in the SDQ to decrease noise. To account for participant-to-participant variability in EMA scoring as well as in trajectories of change in EMA scores over time, we will include a random intercept and random slope for time. All analyses will be conducted on an intent-to-treat basis and will use data from all randomized participants regardless of their level of participation.

A separate model will be fitted to each outcome. Given that this is an exploratory trial, we will not formally adjust for multiple comparisons. However, we will be cautious in our conclusions about any significant findings and will interpret all results in light of all performed analyses.

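### The primary daily outcome has no pre-toy measurement, so the primary model loses precision and change from before the toy cannot be observed

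*Protocol article*

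**What the plan says.** Under Primary Outcome Measure, the protocol article describes a daily parent-rated composite of four items and argues: "By being measured repeatedly over time and within subjects, the items capture the changes in emotional outcomes". Under Outcome Measures it says: "The primary outcome will be a daily EMA measure of child emotion regulation capability (as reported by parents) over a period of 4 weeks".

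In Table 1 the row "Perceived child ER ability" has entries for deployment weeks 1 to 4 and an empty Baseline cell. SDQ, the Emotion Regulation Checklist (ERC), the Difficulties in Emotion Regulation Scale and ER beliefs all have a baseline tick. Study Design and Objectives adds: "The intervention period will start immediately after children receive their arm-appropriate toys". Every daily score is therefore taken after the toy has arrived.

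Data Analyses names one baseline covariate: "The models will adjust for the baseline levels of the score on the total difficulty scale in the SDQ to decrease noise". The target of the model is also given there: "The regression models will examine the difference in the outcome as a function of the assigned condition (Purrble vs active control". On time it states: "we will include a random intercept and random slope for time". Participant Eligibility Criteria requires a "parent-reported score of ≥10 for the total difficulties score on the Strength and Difficulties Questionnaire (SDQ").

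Sample Size and Power uses Cohen d of 0.3, 90% power, alpha .05 and a correlation of 0.75 between repeated measures. It arrives at 92 participants, and at 120 families after inflation and 20% dropout. The Abstract gives 134 children.

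**The concern.** A correlation of 0.75 between days means that most of the variance in a daily score is stable difference between families, including how each parent uses the visual analog scale. A pre-toy value of the same measure is the natural covariate for removing that variance. SDQ total is a weaker stand-in: it is a different and broader instrument, and the entry rule cuts off its lower range. The baseline ERC, one of the instruments from which the daily items were drawn, is collected but is not in the primary model.

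Three things are at stake.

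- **Precision.** The stated power may rest on a covariate that the schedule does not provide.
- **Interpretation.** The logic model's first level is in-the-moment soothing, so part of any effect may already be present at the first report. A child's change from before the toy cannot then be seen.
- **Balance.** The arms cannot be compared at baseline on the primary outcome.

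**Working it through.** **Inputs from the documents.** Effect size d = 0.3, alpha .05, power 90%, correlation 0.75, equal allocation, 20% dropout, and N of 92, 120 and 134.

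**Assumptions.** Two-sided test; 28 daily scores (4 weeks × 7); complete data; compound symmetry. Covariate correlations not given in the documents are marked as assumed.

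**Variance of the 28-day mean**, in units of the daily variance:
V = (1 + 27 × 0.75)/28 = 21.25/28 = 0.759.

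**Per-arm size:** 2 × (1.960 + 1.282)²/0.3² × factor = 233.5 × factor.

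**Reproducing the plan's 92:**
- One pre-toy score of the same outcome as covariate: factor 0.759 − 0.75² = 0.196; 233.5 × 0.196 = 45.9, so 46 per arm and **92** in total. This matches exactly.
- No outcome baseline and no covariate: 233.5 × 0.759 = 177.2, so 178 per arm and **356** in total.
- The only other match found is a repeated-measures between-group F test without a baseline that reads 0.3 as Cohen f (d = 0.6). It also gives 92; with f = 0.15 (d = 0.3) it gives 358.

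The article does not say which route was used. Its description of 0.75 as conservative fits the second, where N rises with the correlation. In the first, N falls from 126 at a correlation of 0.5 to 92 at 0.75.

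**Power for the design as written**, at 96 completers (120 × 0.8), normal approximation; a noncentral t is up to one point lower:

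| Covariate | Factor | Power at 96 | N for 90% |
|---|---|---|---|
| None | 0.759 | 39.2% | 356 |
| SDQ, r = 0.3 with a daily score (assumed) | 0.759 − 0.09 = 0.669 | 43.5% | 314 |
| SDQ, r = 0.6 with a daily score (assumed) | 0.759 − 0.36 = 0.399 | 64.3% | 188 |
| One pre-toy day, r = 0.75 | 0.196 | 91.2% | 92 |

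First row in full: SE = √(4 × 0.759/96) = 0.178; 0.3/0.178 − 1.960 = −0.27, so power is 39%.

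Without an outcome baseline or covariate, the effect detectable with 90% power is 3.242 × √(4 × 0.759/N). That is 0.59 at N = 92 and 0.58 at N = 96.

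**Gain from a run-in if correlation decays.** Take N = 107 (134 × 0.8). Assume that SDQ correlates 0.4 with both the run-in mean and the 28-day mean, and that the run-in mean correlates r = 0.5 to 0.7 with the 28-day mean.
- SDQ alone: factor 0.759 × (1 − 0.16) = 0.638; power about 49%.
- SDQ and run-in: R² = (0.16 + r² − 2 × 0.4 × 0.4 × r)/(1 − 0.16).
  - r = 0.5: R² = 0.250/0.84 = 0.298, factor 0.533, power about 56%.
  - r = 0.7: R² = 0.426/0.84 = 0.507, factor 0.374, power about 71%.

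**Best case.** With fully exchangeable correlation, three pre-toy days give a factor of 0.759 − 0.5625/[(1 + 2 × 0.75)/3] = 0.084, and power above 99% at N = 92. This requires the run-in mean to correlate 0.75/√(0.833 × 0.759) = 0.94 with the 28-day mean.

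**The case against.** The strongest reply is that the primary hypothesis is comparative. It sets Purrble against the control toy, and the model tests a between-arm difference. Randomisation makes that contrast valid without a baseline, and an effect present from the first evening is included in it. The sentence on capturing change can be read as day-to-day change during deployment, which 28 scores with a time slope can show. All of this stands.

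A reader might therefore infer too much from the missing baseline:
- **That the trial cannot show change at all, or is biased.** The documents do not support this. Only change from before the toy is out of reach.
- **That choosing interview families by change in outcome data is undermined.** Postdeployment Interviews defines that change over the primary period, which needs no pre-toy value, and the weekly SDQ and ERC do have baselines.
- **That a run-in would lift power from under 40% to near certainty.** The lower figure ignores the planned SDQ adjustment. The upper one needs exchangeable correlation, and the planned random slope itself allows for departures from that.

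It is also fair to say that the entry rule may narrow the range of the ERC and of a run-in measure, since they are related constructs. Finally, the Results section reports primary data collection finished by mid-May 2021, so a run-in may no longer be possible.

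**Conclusion.** The point holds as a matter of precision and wording, not of bias. No pre-toy value of the primary outcome exists, and the only baseline adjustment is for a different, range-restricted instrument.

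At d = 0.3, power at 96 completers is about 39% unadjusted and about 43–64% with SDQ, well short of the stated 90%. The article's 92 matches either an outcome baseline that is not collected or an effect twice as large as the one named. Under less favourable correlation, a run-in would still raise power at N = 107 from about 49% to about 56–71%.

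These figures rest on compound symmetry within the 28 days, complete daily data, a two-sided test, and assumed correlations for SDQ and the run-in. The random slope and missing days would change them. That a pre-toy score would be the best predictor is an inference from the plan's 0.75, not a documented fact.

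**What to change.** 1. **If families can still be measured before delivery:** send the same four items on 3–7 evenings between the baseline questionnaire and toy delivery, and use their mean as a covariate in the primary model next to SDQ total. The cost is a few evenings of extra burden, later toy delivery, and some missing run-in data that need a handling rule.
2. **In any case, including if collection is over:** add the two baseline ERC subscale scores as covariates in the primary model. They are already collected, so this costs nothing. The precision gained cannot be quantified from the documents.
3. **Wording:** state the primary aim as a between-arm difference in daily ER during deployment, and limit the claim about capturing change to change within those four weeks.
4. **Power:** restate it for the design actually used, saying whether 0.3 is Cohen d or f, which baseline covariate is assumed, and with what correlation. This costs only text and recalculation.
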